### Plans to promote participant retention and complete follow-up

Data will be collected in a single moment, except for ventilator-free days on the 28th day, and brain dysfunction on the 7th and 28th days, which will be evaluated in the review of medical records.

In the event of no informed consent, the patient will not be included in the study.

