### Recruitment

The recruitment phase is set from July 2023 to June 2025. Table 2 details the project’s steps. Septic shock patients starting on noradrenaline, whether newly admitted to or already in the ICU, are potential candidates. However, if an alternative diagnosis emerges within 48 hours, they will be removed from the candidate pool. The multiprofessional team will daily inform the research group about new vasopressor requirements, ensuring rigorous monitoring.

**Table 2 pone.0304412.t002:** Protocol chronology.

		STUDY PERIOD					
	Recruitment	Allocation	Intervention protocol (5 min on each MAP target)			Clinical outcome	
	*07/23–06/25*	*< 48 hours ICU admission*	*MAP 65 mmHg*	*MAP 75 mmHg*	*MAP 85 mmHg*	*7*^*th*^ *day*	*28*^*th*^ *day*

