CA assessment by TCD will use a 2 MHz probe, supported by a helmet frame, the middle cerebral artery will be located through the window of the temporal bone, then it will be confirmed by depth and waveform, and one of the sides will be chosen and will be kept during the protocol. All hemodynamic parameters will be collected simultaneously and transmitted to the Doppler Box through a cable connected to the multiparameter monitor. A B4C sensor will be placed on the contralateral temporal window, which consists of a monitor that quantifies local cranial bone deformations using strain-gauge sensors. The system will be positioned on the frontotemporal region, approximately 3 cm over the first third of the orbitomeatal line, and the software will indicate the wave quality generated. The measurement of ICC will be done using the curve generated by B4C, and P2/P1 > 1 will be considered altered. The quality of measurements will be closely monitored during the duration of recordings to ascertain their acceptability for subsequent stages of off-line analysis.

The instantaneous relationship between arterial blood pressure and CBv will be used to estimate CrCP and RAP for each cardiac cycle using the first harmonic method [18]. Beat-to-beat data will be spline interpolated and resampled at 5 Hz to produce signals with a uniform time base.

Dynamic CA will be assessed using transfer function analysis, using spontaneous fluctuations of MAP as input and corresponding changes in CBv as output in recordings for each MAP target (lasting 5 min), as described previously [19,20]. The Welch method will be adopted for smoothing spectral estimates obtained with the fast Fourier transform (102.4 s segments, 50% superposition) leading to frequency-dependent estimates of coherence, gain and phase. Using the inverse fast Fourier transform, the CBv response to a step change in MAP will also be derived and compared with ten template curves proposed by Tiecks et al. [21] to estimate the ARI [22,23] Baseline cerebral hemodynamic parameters will be reported as the average over a 5-min recording at rest. Values of ARI < 4 will characterize impaired dCA.

The protocol will be interrupted if at any time during the data collection any of the adverse effects, described below, are identified.

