### Statistical methods: Analysis to handle protocol non‑adherence and any statistical methods to handle missing data

After the initial data collection, mechanical ventilator-free days on the 28th day, and brain dysfunction will be recorded. Patients will be included if there is missing data. In the event of missing data, imputation will be performed by calculating the mean of the available data. Patients will be excluded from the study if the quality of the TCD recording is deemed unsatisfactory.

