#### Adverse event reporting and harms

Serious adverse events (SAEs) encompass various potential outcomes, including arrhythmia, intestinal ischemia, and acute extremity ischemia. These events tend to occur more frequently when administering exceedingly high doses of vasopressors, particularly among patients with an imminent prognosis of death within a few hours or those already exhibiting arrhythmias. Consequently, such cases are excluded from the study. Given the anticipated higher mortality rates within this patient cohort, instances of death are not reported as SAEs in this context.

Furthermore, each type of SAE and the total number of SAEs will be reported in the REDCap database and do not have to be reported separately.

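### The protocol promises SAE counts that include intestinal and extremity ischemia, but sets no observation window and its follow-up rule does not collect them after the session

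*Protocol article*

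**What the plan says.** Four places in the protocol article bear on this.

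- **Plans to promote participant retention and complete follow-up.** The rule is "Data will be collected in a single moment, except for ventilator-free days on the 28th day", and the exception continues with "brain dysfunction on the 7th and 28th days, which will be evaluated in the review of medical records". No adverse event is listed.
- **Statistical methods, missing-data section.** It names the same two later items: "After the initial data collection, mechanical ventilator-free days on the 28th day, and brain dysfunction will be recorded".
- **Recruitment, Table 2.** The table has columns for the three MAP targets, day 7 and day 28. Its rows cover cerebral measures, brain dysfunction and ventilator-free days. There is no adverse-event row at any time.
- **Adverse event reporting and harms.** "Serious adverse events (SAEs) encompass various potential outcomes, including arrhythmia, intestinal ischemia, and acute extremity ischemia". It adds that "each type of SAE and the total number of SAEs will be reported in the REDCap database". It gives neither a start nor an end to the period over which events are counted, and it says that deaths are not reported as SAEs.

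The one place that ties adverse effects to a time is in the data collection section: "The protocol will be interrupted if at any time during the data collection any of the adverse effects, described below, are identified". That sentence governs when the session is interrupted.

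**The concern.** The reporting promise and the collection rule do not match. The harms section commits the trial to counts by type for events that include two kinds of ischemia. The follow-up section, the missing-data section and Table 2 then describe what is collected after the session, and none of them includes those events. A site that follows the text would have no prompt to look for ischemia found that evening or the next day, and no time limit telling it whether such an event counts.

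The Sample size section says that this pilot will inform later studies under the same protocol. Its SAE counts are the plan's direct record of harm from stepping MAP up to 85 mmHg. If the report shows few or no ischemic events, a reader cannot tell whether they did not occur or were not looked for.

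**Working it through.** The plan states no SAE rate, window or precision, so there is no figure of its own to reproduce. The check has two parts.

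**1. How long the session is**

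Table 2 gives "Intervention protocol (5 min on each MAP target" for three targets, and the data collection section says "Baseline cerebral hemodynamic parameters will be reported as the average over a 5-min recording at rest". Recording time is therefore 4 × 5 = 20 minutes. The time needed to reach each target is not stated. If it is assumed to be 5 to 15 minutes for each of three steps, the session lasts 20 + 3 × 5 = 35 to 20 + 3 × 15 = 65 minutes.

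**2. What a window closed at the end of the session would record**

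Inputs:
- n = 40 patients, the stated minimum (Study setting).
- p = risk of an ischemic SAE. Assumed 5%, with 2% and 10% as a range. The document gives none.
- m = median delay from exposure to recognition. Assumed 1 to 24 hours, with exponential delays. The document gives none.
- T = length of the window in hours.

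Formulas: share recognised by the end of the window, f = 1 − 2^(−T/m); chance of recording no event, (1 − p·f)^n.

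Example with T = 20 minutes = 1/3 hour, m = 1 hour and p = 5%: f = 1 − 2^(−1/3) = 0.206, and (1 − 0.05 × 0.206)^40 = 0.66.

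| Assumed median delay | Share recognised, 20 min | No event recorded, 20 min | Share recognised, 65 min | No event recorded, 65 min |
|---|---|---|---|---|
| 1 h | 21% | 66% | 53% | 34% |
| 3 h | 7% | 86% | 22% | 64% |
| 6 h | 4% | 93% | 12% | 79% |
| 24 h | 1% | 98% | 3% | 94% |

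With full ascertainment at p = 5%, 40 × 0.05 = 2 events are expected. The chance of recording none is 0.95^40 = 13%, so the chance of at least one is 87%.

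Sensitivity to the assumed risk, with the 20-minute window and delays of 1 to 24 hours:
- At 2%, the chance of recording none is 85% to 99%, against 45% with full ascertainment.
- At 10%, it is 43% to 96%, against 1.5%.

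A reported 0/40 has a one-sided 95% upper limit of 1 − 0.05^(1/40) = 7.2%. That limit is valid only if events were sought over the whole period to which it is taken to apply.

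**The case against.** A reader might infer that data collection ends with the session, that a zero ischemia count is therefore built in whatever the true rate, and that a later event has no way into the database. The document does not support this, for four reasons.

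- No section says that SAE recording stops when the session ends. The harms section sends SAEs to REDCap with no time limit.
- The list in the follow-up section cannot be treated as reliably closed. It omits 28-day mortality, which is a secondary objective and can only be collected later. Table 2 has no mortality row either. The missing-data section names the two items without saying that they are the only ones.
- The sentence on interruption says when to stop the session. It does not say when adverse events are sought.
- That ischemia is recognised late is nowhere in the text, and neither is the 5% risk. The harms section links these events to exceedingly high vasopressor doses, particularly in patients near death or with existing arrhythmia, and says that such cases are excluded.

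These points stand, and they limit the claim. It can also be said that a condensed article may leave the SAE window to a fuller protocol. That would answer simple silence. Here, however, the article states a collection rule with named exceptions, and the rule does not fit the promised counts.

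The other safeguards do not close the gap. Reporting to the Ethics Committee, and auditing of SAE reports with source-data verification, act on events that someone has already recorded. They do not say when or where to look. The day-7 and day-28 record reviews are assigned to other outcomes. Mortality cannot stand in for the SAE count, because deaths are not reported as SAEs.

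**Conclusion.** The concern holds as a mismatch within the text. The follow-up rule names two later items, neither of them an SAE, while the harms section promises SAE counts by type, including ischemia, with no window. If ischemia is often recognised hours after exposure, following the follow-up rule literally would under-record it. With 40 patients, a 5% risk and ascertainment closed at 20 minutes, the chance of recording no event rises from 13% to between 66% and 98%. The size rests on assumed values for risk, delay and closure, and it shrinks if the session is longer or the delay shorter. The conclusion that does not depend on those values is that, with the window undefined, a low or zero ischemia count cannot be interpreted. This should be corrected. It does not show that the trial will miss every ischemic event.

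**What to change.** Reconcile the data collection section, the follow-up section, the missing-data section, the harms section and Table 2, so that they give one SAE window and one source.

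- Add SAEs to the exceptions in the follow-up section and to the later items in the missing-data section, and add an SAE row to Table 2.
- Record whether each named event is already present before the first MAP step.
- Collect new onset, with date and time, during the session and at the day-7 record review already planned.
- Report session and post-session events separately, over all patients in whom a MAP step was started.
- Make clear that the interruption sentence is not the SAE observation window. Its clinical content need not change.

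The cost is a wording change and a few REDCap fields, with no extra visit or test. The downside is attribution. There is no control group, and patients in septic shock on vasopressors may develop ischemia for other reasons. Baseline status and onset time help to describe post-session events but cannot firmly attribute them to the MAP steps, so they should be reported descriptively.

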### Study outcome

The primary endpoint is to assess the impact of different MAP targets on cerebral hemodynamics (ARI, CrCP, RAP by TCD, and P2/P1 by B4C) in patients with septic shock.

Secondary objectives: (1) Evaluate the effects of targeting a MAP of 65 mmHg on cerebral hemodynamics in patients with septic shock. (2) Evaluate the correlation between ARI and B4C. (3) Correlate criteria of clinical severity and neurological dysfunction with cerebral hemodynamics (This will involve assessing the correlation between markers of organ dysfunction such as lactate levels, usage of vasoactive drugs, Sequential Organ Failure Assessment (SOFA) score, and delirium with CA). (4) Assess 28-day mortality.

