#### Composition of the data safety monitoring committee, its role, and reporting structure

This study will undergo monitoring by the local Ethics Committee. Any adverse effects deemed frequent or situations that may cause discomfort to the patient or their representatives will be promptly reported to the Ethics Committee for further evaluation.

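### 28-day mortality is an objective with no stated collection step, mean imputation has no exception for death, and the SAE exemption for deaths has no carve-out around the MAP protocol

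*Protocol article*

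**What the plan says.** All references are to the Protocol article.

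- **Outcome.** Study outcome lists as its last secondary objective "4) Assess 28-day mortality".
- **Follow-up.** Plans to promote participant retention and complete follow-up states that everything is gathered in one session, "except for ventilator-free days on the 28th day, and brain dysfunction on the 7th and 28th days". The source for these later items is given as "which will be evaluated in the review of medical records".
- **Schedule.** Table 2 has clinical-outcome columns for day 7 and day 28. The only marks in them are for brain dysfunction (both days) and ventilation-free days (day 28).
- **Missing data.** The missing-data section names the same two later items and sets one rule: "In the event of missing data, imputation will be performed by calculating the mean of the available data".
- **Safety.** Adverse event reporting and harms expects high mortality and says that "instances of death are not reported as SAEs in this context". SAE types and totals "will be reported in the REDCap database and do not have to be reported separately". Interim analysis says that adverse effects go to the Ethics Committee. The section on the data safety monitoring committee says that adverse effects judged frequent, or situations that may cause discomfort, are "promptly reported to the Ethics Committee for further evaluation".

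**The concern.** A named outcome should appear wherever the protocol lists what is collected. Here three lists agree with one another and omit it. The follow-up sentence is exclusive in form (one session, with two stated exceptions), so the gap cannot be put down to a journal article's brevity.

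Two further rules bear on the same patients. Someone who dies before day 7 or day 28 has no brain status on that day, and the only written rule for an absent value is to fill in the mean of those who have one. The SAE rule exempts every death, whatever its timing relative to the induced pressure change.

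At stake are the completeness of 28-day mortality, the meaning of the day-7 and day-28 variables in a population whose mortality the protocol itself expects to be high, and the visibility of a death close to the study procedure.

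**Working it through.** The document gives no figure to reproduce: it has no event-rate, power or sample-size calculation. The check is a comparison of passages, followed by a conditional illustration.

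**1. Outcome against collection steps**

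| Item | Study outcome | Follow-up section | Table 2, day 7/28 | Missing-data section |
|---|---|---|---|---|
| 28-day mortality | listed | absent | absent | absent |
| Ventilator-free days, day 28 | absent | listed | marked | listed |
| Brain dysfunction, later assessment | neurological dysfunction, no day given | days 7 and 28 | days 7 and 28 | listed, no day given |

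The mismatch runs both ways: mortality is an outcome without a collection step, and ventilator-free days are collected without being a listed outcome.

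**2. What record review can supply**

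A chart read for ventilator-free days to day 28 would normally show a death in hospital. The document describes no contact after discharge, and the objective is 28-day mortality, not in-hospital mortality. The firm gaps are the missing data item and deaths after discharge.

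**3. Effect of the imputation rule, if values of the dead are classed as missing**

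Input from the document: at least 40 patients (Study setting), so N = 40. Assumptions, because the document gives no figures: mortality m of 20% to 50%; survivors' mean ventilator-free days μ of 15 or 20; brain dysfunction in 30% of survivors. The comparator, death scored as 0 days, is also a choice made for this illustration.

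- Dead d = N × m; survivors s = N − d.
- Mean after imputation = μ, whatever the mortality.
- Mean with death scored 0 = μ × s/N, so the difference is μ × m.
- Standard error after imputation, relative to survivors only = √[(s − 1)/(N − 1)] × √(s/N). The standard deviation cancels.
- Death or dysfunction = (d + 0.30 × s)/N.

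| m | d | s | Difference, μ = 15 | Difference, μ = 20 | SE ratio | Death or dysfunction |
|---|---|---|---|---|---|---|
| 20% | 8 | 32 | 3.0 days | 4.0 days | 0.80 | 44% |
| 30% | 12 | 28 | 4.5 days | 6.0 days | 0.70 | 51% |
| 40% | 16 | 24 | 6.0 days | 8.0 days | 0.60 | 58% |
| 50% | 20 | 20 | 7.5 days | 10.0 days | 0.49 | 65% |

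Example at 40% and μ = 20: imputation reports 20 days; scoring death as 0 gives 20 × 24/40 = 12 days; the difference is 8 days. The imputed standard error is √(23/39) × √(24/40) = 0.60 of the survivors-only value.

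For yes/no brain dysfunction, the imputed value is a fraction (0.30 here), which is not a valid status for any patient. The reported rate stays at 30% at every mortality level.

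**4. Safety passages side by side**

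The SAE section exempts all deaths because mortality is expected to be high, and adds that patients close to death are excluded. Table 1 likewise excludes patients at imminent risk of death. A death during or just after the MAP protocol in an eligible patient is therefore not clearly covered by the stated reason, yet the exemption applies to it. The same section says that SAEs logged in REDCap need no separate report. Interim analysis and the monitoring section describe a route to the Ethics Committee, the latter only for frequent or discomforting effects. How these three passages fit together is not stated.

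**The case against.** A reader might infer that deaths are lost altogether and that the mortality objective cannot be answered. The document does not support that. Charts are reviewed to day 28, in-hospital deaths would normally be seen there, mortality is a named outcome, and the auditing section provides for monitoring of endpoint recording and source-data verification. Fig 2, the participant timeline, is not shown and may list mortality. What remains is that the written follow-up list and schedule omit it, and that no step is given for discharged patients.

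A reader might also infer that survivors' values will stand in for the dead. No passage classes a dead patient's values as missing, and ventilator-free days are not defined, so a definition in the full protocol or analysis plan may already score death. That makes the imputation effect conditional. It does not remove the point that the published rule has no exception and directly follows the sentence naming these two variables.

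The table of days rests on assumed inputs and concerns a variable that Study outcome does not list. The primary measures (ARI, CrCP, RAP, P2/P1) come from a single session and are untouched, and all secondary outcomes are declared exploratory. This is accepted in full.

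On safety, it would be too strong to say that a procedure-related death reaches no overseer. Arrhythmia and ischaemic events remain SAEs even if the patient then dies, adverse effects interrupt the protocol, and a route to the Ethics Committee exists. The reporting passages use different terms (adverse effects against SAEs), so they are unclear against one another and not in flat contradiction. What stands is that no rule makes a death near the procedure reportable in itself.

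**Conclusion.** The point holds in a limited form.

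- **Firm:** 28-day mortality is an objective, but vital status is absent from the closed follow-up list, Table 2 and the missing-data section, and no stated step captures deaths after discharge.
- **Conditional:** if the later values of patients who died are treated as missing, the unqualified rule substitutes survivors' means. On the stated assumptions this raises mean ventilator-free days by 3 to 10 days against a zero score for death, shrinks the nominal standard error to between 0.80 and 0.49 of the survivors-only value, and gives an invalid fractional status for brain dysfunction. The real size depends on mortality and survivors' values that the document does not give.
- **Firm but narrow:** the SAE exemption has no carve-out for deaths during or shortly after the MAP protocol, and the reporting route needs clarifying.

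Only secondary or exploratory outcomes and safety reporting are affected. The correction should be made, but the primary analysis does not depend on it.

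**What to change.** 1. Add vital status and date of death to day 28 to the follow-up section and Table 2, from record review or by a call if the patient has been discharged.
2. Exclude values truncated by death from mean imputation. State how death is handled in each later variable: for example, 0 ventilator-free days for death by day 28, and brain dysfunction at days 7 and 28 reported as dead, alive with dysfunction, or alive without it.
3. Report deaths during the MAP protocol, or within a stated window after it, to the Ethics Committee.
4. Reconcile Interim analysis, the data safety monitoring committee section, and Adverse event reporting and harms, so that it is clear which events go to the Ethics Committee and which are only logged in REDCap.

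Cost: two form fields, some calls to discharged patients, a few more reports and some redrafting. The measurement session does not change.

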** *ASSESSMENTS* **							
**Sex, age, time, time since admission to the ICU, infection site, comorbidities, APACHE, SOFA, vasopressor dosage, blood analysis**		x					
**TCD: ARI, CrCP, RAP**			X	X	X		
**B4C: P2/P1 ratio**			X	X	X		
**Brain dysfunction**		X				x	x
**Ventilation free days**							x

MAP: Mean arterial pressure, MCA: Middle cerebral artery, TCD: Transcranial doppler, B4C: Brain4care, ICU: Intensive care unit, APACHE: Acute Physiologic and Chronic Health Evaluation, SOFA: Sequential Organ Failure Assessment, ARI: Autoregulation index CrCP: Critical closing pressure, RAP: Resistance-area product.

The locals researchers will be designated for daily data collection and interactions with patients or their families after the, ensuring that recruitment is possible within 48 hours from the onset of vasopressor therapy to optimize data gathering.

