## Methods: Data collection and management

Data collection on admission will include the following: demographic characteristics, comorbidities, source of infection, Sequential Organ Failure Assessment at ICU admission, temperature, hemogram lactate, hepatic and renal markers, Glasgow Coma scale or Richmond Agitation Sedation Scale, Confusion Assessment Method for the ICU scale, drug for sedation, neuromuscular blocking agents, mechanical ventilation, quantify vasoactive drug dose on collection day, arterial blood gasses before and after the protocol, presence of acute cardiac dysfunction by echocardiography and left ventricle ejection fraction. We will describe the utilization of antipsychotics or sleep-improving medications before ICU admission.

At the time of data collection, the presence of brain dysfunction associated with sepsis will be assessed by: a Glasgow scale score < 15 or when disorientation, disorganized thinking, or agitation are reported by the attending physician, regardless of sedative/analgesic use and in the absence of neurological disease (i.e., dementia, cerebrovascular disease, brain tumors, previous traumatic brain injury). Data from medical records will be used to access such information, the description of the change in the level of consciousness or the use of antipsychotics or dexmedetomidine will be interpreted as a brain dysfunction.

Systemic physiological monitoring will be performed by an arterial line, cardioscopy, pulse oximetry, and capnography (if unavailable at the time of collection, this will be described). Before starting the monitoring, the proper functioning of the arterial line will be confirmed and the site described.

Each patient will adhere to a uniform protocol where, after establishing baseline measures, the mean arterial pressure (MAP) targets will be sequentially increased in the order of 65, 75, and then 85 mmHg. This structured approach ensures sample homogeneity.

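### Day-7 and day-28 brain dysfunction is a yes/no item read only from records, and the blanket mean-imputation rule would give any patient without an entry a fractional value

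*Protocol article*

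**What the plan says.** The section on retention and follow-up says that data are collected at one moment, with two exceptions: ventilator-free days at day 28, and "brain dysfunction on the 7th and 28th days, which will be evaluated in the review of medical records". It mentions no visit, call or other contact. The assessments part of Table 2 lists "Brain dysfunction" at allocation and at days 7 and 28.

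The section on data collection and management defines the item by presence: "the presence of brain dysfunction associated with sepsis will be assessed by: a Glasgow scale score < 15", or certain physician-reported signs. When records are read, a described change in consciousness counts as positive, and so does drug use: "the use of antipsychotics or dexmedetomidine will be interpreted as a brain dysfunction". Nothing says whether a record with no entry for the day means absent or missing.

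The missing-data section opens by naming the follow-up items ("mechanical ventilator-free days on the 28th day, and brain dysfunction will be recorded"). It then states "Patients will be included if there is missing data" and "In the event of missing data, imputation will be performed by calculating the mean of the available data". No variable is exempted.

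On deaths, the harms section says: "Given the anticipated higher mortality rates within this patient cohort, instances of death are not reported as SAEs in this context". Mortality at 28 days is a secondary objective, but no rule says what brain-dysfunction status a dead patient has at day 7 or 28.

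**The concern.** A status tied to a calendar day and read from a chart needs someone to have observed the patient on that day. Patients who have left hospital alive, or who have died, may have no such entry. The reasons for the gap, often recovery or death, are closely related to the item itself.

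Filling the gap with a mean does two things. It puts a proportion where only yes or no makes sense, and it takes that proportion from the patients still under observation. Days 7 and 28 are the only scheduled neurological assessments after the bedside session. At stake are the reported frequency of brain dysfunction at follow-up and any relation between that status and ARI or P2/P1.

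**Working it through.** The article gives no discharge rate, missing-data rate or brain-dysfunction rate, so there is no stated figure to reproduce. What follows is an illustration under assumed inputs.

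**Inputs**
- N = 40, the minimum under Study setting.
- d: share of patients without a record for the day. Assumed 0.10 to 0.60.
- p_in: dysfunction rate among those with a record. Assumed 0.30 to 0.70.
- p_out: rate among those without a record. Assumed 0 up to p_in.
- The imputation rule is read as the mean over patients who have a value.

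**Step 1: bias among survivors, deaths set aside**
- Rate after imputation = p_in.
- True rate = (1 − d) × p_in + d × p_out.
- Bias = d × (p_in − p_out).

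With p_in = 0.50:

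| d | True rate, p_out = 0 | Bias (points) | True rate, p_out = 0.10 | Bias (points) |
|---|---|---|---|---|
| 0.10 | 45% | 5 | 46% | 4 |
| 0.25 | 37.5% | 12.5 | 40% | 10 |
| 0.50 | 25% | 25 | 30% | 20 |
| 0.60 | 20% | 30 | 26% | 24 |

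Over all the assumed ranges the bias runs from 0 (p_out = p_in) to 0.60 × (0.70 − 0) = 42 points.

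**Step 2: precision**
- Naive SE after imputation = sqrt(n_obs × p(1 − p) / ((N − 1) × N)).
- SE from observed patients only = sqrt(p(1 − p) / n_obs).
- Ratio = n_obs / sqrt(N(N − 1)). With N = 40 this is 36/39.5 = 0.91 at d = 0.10, 30/39.5 = 0.76 at d = 0.25 and 20/39.5 = 0.51 at d = 0.50.

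The imputed values add apparent precision without adding information.

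**Step 3: deaths included**

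Assume 40 patients: 12 dead, 14 discharged without dysfunction, 14 in hospital of whom 7 have dysfunction.
- After imputation: 7/14 = 50% for everyone.
- Among survivors: 7/28 = 25%.
- If death counts as a bad outcome: (7 + 12)/40 = 47.5%.

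The imputed 50% is far above the second figure and close to the third. The direction therefore depends on what the rate is meant to describe, and the article does not define that.

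**Step 4: association**

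In the same example 12 + 14 = 26 of 40 patients carry the identical value 0.5. That value equals the overall mean, so these patients add nothing to the numerator of a regression slope of status on ARI or P2/P1, while their spread in ARI or P2/P1 still enters the denominator. If that spread is similar in both groups, the slope shrinks to about 14/40 = 0.35 of its observed-only value, and the correlation to about sqrt(0.35) = 0.59. The contrast between discharged and dead patients is lost completely.

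**Step 5: the other coding**

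If a discharged patient with no entry is coded absent, nothing is imputed for that patient and Step 1 does not apply. Dysfunction after discharge may then be under-counted.

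**The case against.** A reader might infer that records end at discharge, that recovered patients therefore have no value, and that the plan as written assigns them the rate of sicker inpatients and so overstates persistent dysfunction. The article does not support this as fact. It never says that records stop at discharge or that discharged patients are coded missing. Because dysfunction is read from positive entries, coding them absent is an equally open reading. Nor has every discharged patient recovered; transfers are possible. Deaths fall under the same imputation rule, so the overall direction is not established. Every rate in the illustration is assumed.

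The importance is also limited. Day-7 and day-28 status is not a named endpoint. The secondary objective on clinical severity and neurological dysfunction lists lactate, vasoactive drugs, SOFA and delirium without naming either day, and brain dysfunction is also assessed at the time of data collection, so that objective can be met without the follow-up values. Secondary outcomes are declared exploratory, in a pilot.

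All of that stands. It can also be said that coding of discharged patients belongs in the full protocol or the collection form. That is fair for the coding, but not for the imputation: the article states that rule itself, directly after naming brain dysfunction, and as stated it does not suit a yes/no item.

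**Conclusion.** The point holds in conditional form. Records are the only named source for a yes/no status on two fixed days, and a stated rule would replace any missing value of it with a proportion. If patients discharged or dead by then are treated as missing, the survivor rate is overstated by d × (p_in − p_out): 0 to 42 points over the assumed ranges, and nil if the rates match or if discharged patients are coded absent. This takes discharged patients to do no worse than those still in hospital. With deaths included, the direction of bias in the overall rate cannot be stated, but loss of association follows from the identical value given to opposite courses. The effect is confined to an exploratory follow-up variable. ARI, CrCP, RAP and P2/P1 come from the bedside session and are untouched by this point.

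**What to change.** - **Retention and follow-up section:** define the assessment as day 7 or day 28, or the day of live hospital discharge if earlier, scored from the last documented status in the record. Record the discharge date and vital status.
- **Reporting:** show four separate categories at each day: in hospital with dysfunction, in hospital without dysfunction, discharged alive (with status at discharge), and dead.
- **Missing-data section:** exempt this binary item from mean imputation, for deceased as well as discharged patients.
- **Associations:** in any analysis relating follow-up brain dysfunction to cerebral hemodynamics, use status at discharge or on the fixed day among survivors, and show death separately.

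The cost is rewording in two sections and a few REDCap fields filled from the record review already planned; 28-day mortality is already an objective. The small downside is that status at discharge is taken earlier than day 28 and misses later change.
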